### Recruitment

Patients are recruited by staff at the cancer centers according to predefined inclusion and exclusion criteria. The consortium lead is implementing strategies for adequate participant enrolment by actively supporting centers in the establishment of adequate structures and by regularly providing feedback on recruitment data provided by the evaluation team. Recruitment for interviews will continue until thematic saturation is reached, guided by the concepts of thematic saturation (11) and information power (12).

#### Eligibility criteria

Patients with severe, advanced cancer who have undergone guideline-conformant therapy and those with rare tumors for which no guideline-conformant therapy exists.

Inclusion criteria:
Diagnosis of cancer, including progression or recurrence (all cancer types can be included)Patients are capable of participating in data collectionTreatment at one of the participating CCC/ZPMs or patients seeking a second opinion thereMolecular diagnostics are possiblePatient qualifies for the MTB of the centerFirst presentation at the MTB of the centerPatients aged 18 years or olderInformed consent—written consent for participation in the study and data sharing

#### Exclusion criteria

Language or cognitive impairments that prevent data collection even with support

### Interventions

#### Explanation for the choice of comparators

The comparator consists of centers that have not yet completed the certification process to reflect the state of care prior to certification and to show the improvement in process-related and medical outcomes once the DNPM standard is established in the respective cancer center. Control patients at the sites meet the criteria for inclusion in the MTB but are not certified according to the standards of the DNPM in the MTB. The DNPM standard includes quality-assured molecular diagnostics as well as evidence-based treatment recommendations in interdisciplinary MTBs. Therapies initiated at the sites may vary individually by timing, duration, and type.

### Criteria for discontinuing or modifying allocated interventions

The trial will be discontinued for a given trial participant in case the patient withdraws his or her informed consent or in the case of his or her death. Modification of interventions is not applicable as the intervention is implemented in centers, not in specific patients.

### Strategies to improve adherence to interventions

Regular meetings will be held with study staff from all participating centers to improve data collection and documentation. Feedback from the centers will also be used to improve the design of the database and its interface. Besides this, all steps of the data collection will be regularly outlined at steering committee meetings, where all centers are present to ensure that centers understand the purpose of questionnaires, interviews, focus groups, etc. Next to this, updates on case numbers will be given regularly in these meetings to ensure that centers meet their recruitment goals. Additionally, questionnaires will be piloted with study staff in order to ensure that these are relevant to their daily work and are well understood.

### Outcomes

A central element is the primary endpoint at the patient level (micro-level), which is divided into a three-tiered endpoint and allows conclusions about the benefits of the intervention. Tier 1 includes the frequency of access to the new form of care; Tiers 2 and 3 encompass the development and implementation of therapy proposals. The quantitative evaluation is supplemented by a quantitative patient survey using validated questionnaire instruments and a health economic assessment. In addition to quantitative data collection, interviews with patients are conducted to capture patient understanding of and expectations regarding personalized medicine. Overall, the development and enhancement of structures and processes in centers for personalized medicine (ZPM) is documented through standardized self-report questionnaires (see Appendix 2), as well as interviews and focus groups. This also specifically captures the exchange and knowledge transfer between ZPMs, as well as the extent to which an exchange of harmonized data has taken place. A complete list of the measures used in the quantitative and qualitative process evaluation, as well as secondary patient-related endpoints (clinical: response, PFS, OS, toxicity, patient questionnaires, and health economic measures), is presented in Table 2. A design diagram further elaborating on the data collection time points can be found in Appendix 3.

**Table 2 T2:** Primary and secondary endpoints and data collection.

Level	Evaluation	Primary endpoint	Time point	Instrument
Micro-level	Quantitative evaluation	Change in patient management based on the decision of the tumor board (assessed on three tiers):		Based on a quantitative questionnaire filled out by staff on site *(included in the provider questionnaire)*
		Tier 1: number of patients admitted to the tumor board	T0 = day of initial presentation at the tumor board)	
		Tier 2: proportion of patients with changed diagnostic strategy and/or therapy recommendation due to the decisions of the tumor board	T1 = day of therapy decision	
		Tier 3: proportion of patients with an actually implemented changed diagnostic strategy and/or therapy	T2 = day of the first therapeutic intervention	
		Secondary endpoints		
Micro-level	Quantitative evaluation	Clinical data of patients treated in the MTB • Response • Progression-free survival • Overall survival • Toxicities	event-driven	*Included in the provider questionnaire*
		Patient satisfaction and quality of life of patients treated in the MTB • Satisfaction • Quality of life	At study enrollment, 2–3 months after enrollment, and 5–6 months after enrollment	• Modified questionnaire instrument based on the PSCC-G instrument • Established questionnaire instruments for disease-specific quality of life, EQ-5D-5L, and EORTC QLQ-C30 *(included in the patient questionnaire)*
		Health economics • QALYs • Total costs (healthcare costs, intervention costs) • ICER	5–6 months after enrollment	• EQ-5D-5L • Modified FIMA questionnaire • Controlling the data of participating university hospitals • Survey of centers *(included in patient questionnaire)*
	Qualitative evaluation	Patient-level survey: • Understanding and attitude toward personalized medicine • Qualitative assessment of the implementation processes • Expectations regarding care provided by the personalized medicine services (ZPMs)/the decentralized personalized medicine (DNPM) • Perceived care before and during treatment with ZPMs/DNPM • Costs incurred in the context of personalized medicine care	At a later stage in the project	Semi-structured interviews with patients
Meso-level and macro-level	Process evaluation (quantitative)	Perspective of staff from centers for personalized medicine (ZPMs): • Degree of standardization of processes • Establishment of new coordination processes at the medical or professional level (e.g., expert committees) • Implementation and structural costs (costs incurred from transitioning to ZPM/DNPM) • Process costs (ongoing costs before ZPM, or of the individual ZPMs) • Exchange/knowledge transfer between ZPM • Exchange of harmonized data • Presence of interconnected data structures (e.g., completeness, quality) • Exchange of harmonized data between the ZPMs • Communication and decision-making structures and processes	• T0: at the time of certification • T1: at an intermediate stage in the project • T2: at a later stage in the project	Quantitative questionnaire based on the certification forms at the center, participation in meetings of the MTB working group, and analysis of the working group’s meeting minutes *(organizational structure and process survey)*
	Process evaluation (qualitative)	Perspective of staff from centers for personalized medicine (ZPMs): • Attitudes and experiences regarding and with personalized medicine • Attitudes toward and experiences with the change processes • Satisfaction of the involved staff • Planning and adaptations in the implementation process • Possible barriers and facilitators in the implementation process • Perceived added value of the new form of care • Exchange/knowledge transfer between ZPM • Exchange of harmonized data • Presence of interconnected data structures (e.g., completeness, quality) • Exchange of harmonized data between the ZPMs • Communication and decision-making structures and processes	At an intermediate stage in the project	Semi-structured interviews with staff from centers for personalized medicine, participation in meetings of the MTB working group, and analysis of the working group’s meeting minutes
	Process evaluation (qualitative)	Perspective of staff from centers for personalized medicine (ZPMs): • Planning and adaptations in the implementation process • Possible barriers and facilitators in the implementation process • Perceived added value of the new form of care	At a later stage in the project	Provider focus groups

### Participant timeline

Table 3 shows the participant schedule throughout the intervention period.

**Table 3 T3:** Participant schedule.

Specification of data collected	Participant schedule			
	Enrolment	2–3 months post-enrolment	5–6 months post-enrolment	Close-out
Time point/assessment	T0	T1	T2	T3
Study participation				
Eligibility screen	X			
Informed consent	X			
Allocation	X			
Clinical data collection				
Socio demographics	X			
Diagnose	X	X	X	
(Further) therapies in the last 3 months outside the MTB recommendation	X	X	X	
MTB recommendations		X	X	
Follow-up on MTB recommendations		X	X	
Scheduled end (follow-up completed after 5–6 months)				X
Reason for premature end				X
Patient questionnaire				
Socio demographics	X	X	X	
Living situation	X	X	X	
Financial Situation	X	X	X	
Social support	X	X	X	
EQ-5D-5L (health-related quality of life)	X	X	X	
EORTC QLQ-C30 (disease-related quality of life)	X	X	X	
FIMA (Utilization of health services)	X	X	X	
Patient satisfaction	X	X	X	
Patient interviews				
Understanding, expectations, and attitudes toward PM, perceived care		X	X	

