### Sample size

The study aims to recruit a total of 4,807 patients, including 3,507 in the intervention group and 1,300 in the control group. The following assumptions underlie the sample size estimation: For nine newly established ZPMs (centers), two centers would be acceptable as dropouts. At least four existing centers in BW are considered unlikely to drop out, and seven newly initiated ZPMs serve as the basis for the sample size estimation. The new centers will contribute to controlling/intervening patients before/after initiation as ZPM, while the existing ZPM will only have intervention patients. This approach, inspired by the stepped-wedge design, has already been successfully used in several projects funded by the Innovation Fund (10). An average stay of 6 months in the control phase is assumed. It is estimated that each comprehensive cancer center (CCC) will have between 300 and 500 patients with PM, resulting conservatively in 1,300 control patients. This is compared with an estimated 3,500 ZPM patients from existing ZPM and those newly implemented during the study period. With these numbers, ignoring the cluster effect, differences of approximately 5% can be detected in the chi-squared test (Type I error 5% two-sided) with a power of >80% (exactly 86%) and differences of 7% with >90% (exactly 96%) power. Assuming a variance inflation due to cluster effects of 2, differences of 7% can still be detected with 85% power, and with very high cluster effects of 4 or 6, differences of 10% or 13% can be detected with 85% power.

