### Data collection and management

#### Quantitative evaluation

The primary endpoint contains three tiers. At Tier 1, the primary endpoint is the number of patients who receive an indication-driven, standardized access to the new form of care—personalized diagnostics and therapy—defined as access to the MTB. For this endpoint, a standardized data collection instrument will be developed to document both the original procedure and the newly implemented one, including the extent of the changes made (e.g., additional molecular diagnostics and therapy). The new procedure will be based on predefined, evidence-based criteria established by the ZPM network in BW. At Tier 2, it will be assessed for which patients the diagnostic process or diagnostic interpretation was significantly changed. Among this group, Tier 3 evaluates the proportion of patients for whom the changes ultimately led to treatment within the framework of personalized medicine. These changes may also include recommendations for genetic counseling, which—although not directly involving therapy or additional diagnostics—represent a modification in patient care.

Secondary clinical endpoints will be assessed continuously during the study: Adverse events (AEs) and serious adverse events (SAEs) will be recorded as they occur, and overall survival (OS) and progression-free survival (PFS) will be recorded every 6 months (T4–T8) until the end of the observation period, with a minimum follow-up of 6 months and an average follow-up of 12 months.

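### Tables 2 and 3 time the primary endpoint differently, and the rules on death and missing data put Tier 2 and Tier 3 values of early deaths at risk of being imputed

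*Protocol article*

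**What the plan says.** **Outcomes, Table 2.** Tier 1 is set at T0, the first presentation at the board. Tier 2 carries the time point "T1 = day of therapy decision" and Tier 3 "T2 = day of the first therapeutic intervention". The source is a questionnaire completed by site staff.

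**Participant timeline, Table 3.** T0 is enrolment, T1 is 2–3 months and T2 is 5–6 months. The rows for MTB recommendations and "Follow-up on MTB recommendations" are marked at T1 and T2 only. The clinical entries at enrolment are sociodemographics, diagnosis and recent therapies. A close-out column holds the reason for a premature end.

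**Data collection and management, Quantitative evaluation.** The article promises that "a standardized data collection instrument will be developed to document both the original procedure and the newly implemented one", without saying when the original procedure is entered. Tier 3 is assessed within the group that has a Tier 2 change.

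**Criteria for discontinuing.** The trial ends for a participant on withdrawal of "informed consent or in the case of his or her death".

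**Missing data, Quantitative evaluation.** Multiple imputation is planned under missing at random. Centre and centre status are predictors; diagnostic class and disease severity are to be considered. Death is not mentioned.

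**Timeline of the study.** Recruitment closed on 30 September 2024, and data collection was expected to run to the end of November 2025.

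**The concern.** Tier 2 is a change from a plan, so it is sound only if that plan was fixed before the board decided. A site that follows Table 2 records Tier 2 on the decision day. A site that follows Table 3 may first do so 2–3 months later, with staff who know the decision and the centre's certification status. Certified centres document MTB decisions in about 40 harmonised parameters, whereas control practice is site-specific. Late reconstruction could therefore draw on different records in the two arms, and an error in Tier 2 carries into Tier 3.

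The second issue is early death in a population with severe, advanced cancer. Taken literally, the schedule, the discontinuation rule and the imputation rule together leave Tiers 2 and 3 blank for a patient who dies before the first documentation, and then fill them with values modelled on patients who lived. Neither value is truly unknown: the board's decision exists, and a patient who died before any implementation is a Tier 3 no.

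**Working it through.** **1. The plan's own scale.** The Sample size section gives "a total of 4,807 patients, including 3,507 in the intervention group and 1,300 in the control group", a two-sided 5% chi-squared test, and 86% power for 5 points without clustering. No base rate is stated, so it was scanned from 2% to 94%. The formula is power = Φ[(Δ − 1.96·√(p̄(1−p̄)(1/n₁+1/n₂))) / √(p₁(1−p₁)/n₁ + p₂(1−p₂)/n₂)].

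- 5 points, 47.5% vs 52.5%: (0.05 − 0.0318)/0.0162 = 1.12, power 86.9%, the lowest in the scan. The stated 86% reproduces.
- 7 points, variance inflation 2: 86.3% at its lowest. The stated 85% reproduces.
- 7 points without clustering: at least 99.1%, where the article states "differences of 7% with >90% (exactly 96%) power". This figure does not reproduce at any base rate, but it is conservative and has no bearing here.

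The yardstick for bias is therefore a between-arm difference of 5 to 7 points.

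**2. The two schedules side by side.**

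| Item | Table 2 | Table 3 |
|---|---|---|
| T1 | therapy decision | 2–3 months after enrolment |
| T2 | first therapeutic intervention | 5–6 months after enrolment |
| Original plan | implied by the word change | no row |
| Patient never treated | no T2 day | T2 still exists |

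**3. How many patients could be affected.** The documents give no death rate, so the median survival is an assumption. With exponential survival, the share dead by 2.5 months is 1 − 2^(−2.5/m).

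- m = 8 months: 0.195, × 4,807 = about 936
- m = 12 months: 0.134, about 646
- m = 16 months: 0.103, about 493

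**4. Tier 3 error in level.** Assume 15% early deaths, implementation in 30% of survivors and 10% of early deaths, and imputation that reproduces the survivors' rate. The truth is 0.85×0.30 + 0.15×0.10 = 27%; the imputed figure is 30%. This 3-point error is in one group's level.

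**5. Tier 3 error in the difference, equal early mortality.** If survivors differ by d and early deaths do not differ by arm, the true difference is 0.85d while imputation gives d.

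- d = 5: true 4.25, error 0.75 points
- d = 7: true 5.95, error 1.05 points
- Over the range in step 3: 0.103×5 = 0.5 to 0.195×7 = 1.4 points

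**6. Tier 3 error in the difference, unequal early mortality.** With no arm effect among survivors, the error is (difference in early-death share) × (survivor rate − early-death rate). For 20% vs 10% early deaths, 0.10×(0.30−0.10) = 2 points; with a survivor rate of 40%, 0.10×(0.40−0.10) = 3 points.

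**7. Tier 2 labelling.** If 60% of plans are truly unchanged and the two arms wrongly call 5% and 10% of these changed, the spurious difference is 0.60×(0.10−0.05) = 3 points. All three inputs are assumptions, and the documents do not indicate a direction.

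**The case against.** A reader might infer that early deaths have no primary outcome at all. The documents do not support that. Tier 1 is fixed at the first presentation, and Tiers 2 and 3 come from site staff, who also record deaths (Health economic evaluation) and can enter a board decision after the patient has died. The discontinuation rule does not say that entry of earlier events stops. The values are at risk, not certainly lost.

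A reader might also infer that the original plan is never recorded and that Tier 2 is judged in hindsight. An instrument for the original procedure is planned, and only its timing is open. The abstract describes the primary data as prospectively collected, and Table 2 dates Tier 2 to the decision. Table 3 could be read as giving documentation windows for events that Table 2 dates. That is a fair reading, but the article does not state it, and the shared labels work against it.

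It can further be said that the tiers are analysed as yes/no, so an untreated patient can simply be a no; that disease severity may enter the imputation model; and that the handling of death is often left to an SAP. These points soften the concern. They do not settle the contradiction between the two printed tables, and an analysis plan cannot recreate a prior plan that no dated record holds.

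Finally, the 3-point level error should not be set directly against planned differences of 5 to 7 points. With equal early mortality most of it cancels.

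**Conclusion.** The point holds as an inconsistency in how the primary endpoint is timed, with an unresolved consequence for early deaths. Tables 2 and 3 must be reconciled, the original-procedure record needs a place before the board decision, and the rules on death and imputation should not be left to act together as written.

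The size of any bias in the between-arm difference is unknown. With 15% early deaths in both arms, 10% implementation among them, and imputation at survivors' rates, it is about 1 point or less (0.75 to 1.05), and up to 1.4 at the extreme of the assumed range. Two to 3 points require early mortality or documentation to differ by arm. That is possible because transition is not randomised, but nothing in the article shows it. All survival, implementation and misclassification rates used here are assumptions.

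**What to change.** Reconcile Table 2, Table 3, the discontinuation rule and the text on the original procedure, and give the labels T1 and T2 one meaning each.

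- **Tier 2.** Compare the dated MTB decision with the plan in the dated MTB referral, in the same way in both arms. As recruitment has closed, this means abstraction from existing records; a new enrolment field would reach nobody. Report by arm how often no plan is recorded.
- **Tier 3.** Define it for every patient as implemented yes/no by one fixed time that the existing 5–6 month documentation covers.
- **Deaths.** Complete both tiers from records for patients who died. Count death before implementation as not implemented, and exclude it from imputation. Report early deaths by arm beside the result.

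The cost is an amendment of two tables and two short passages, plus some record abstraction; no extra visit is needed. Two drawbacks remain. Tier 2 stays missing where the referral states no plan, possibly more often in the non-harmonised control phase, which is why it should be reported by arm. Changes implemented after the fixed time count as no.

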### Data collection and management

#### Quantitative evaluation

The primary endpoint contains three tiers. At Tier 1, the primary endpoint is the number of patients who receive an indication-driven, standardized access to the new form of care—personalized diagnostics and therapy—defined as access to the MTB. For this endpoint, a standardized data collection instrument will be developed to document both the original procedure and the newly implemented one, including the extent of the changes made (e.g., additional molecular diagnostics and therapy). The new procedure will be based on predefined, evidence-based criteria established by the ZPM network in BW. At Tier 2, it will be assessed for which patients the diagnostic process or diagnostic interpretation was significantly changed. Among this group, Tier 3 evaluates the proportion of patients for whom the changes ultimately led to treatment within the framework of personalized medicine. These changes may also include recommendations for genetic counseling, which—although not directly involving therapy or additional diagnostics—represent a modification in patient care.

Secondary clinical endpoints will be assessed continuously during the study: Adverse events (AEs) and serious adverse events (SAEs) will be recorded as they occur, and overall survival (OS) and progression-free survival (PFS) will be recorded every 6 months (T4–T8) until the end of the observation period, with a minimum follow-up of 6 months and an average follow-up of 12 months.

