**Methods:**

The DNPM project is evaluated as a Hybrid Type 3 implementation study using a non-randomized, modified stepped-wedge design. Twenty-one university hospital sites across Germany will transition from standard, non-harmonized care to a harmonized personalized medicine intervention at different time points, based on administrative readiness indicated by certification. The primary outcome is change in patient management due to molecular tumor board (MTB) decisions, assessed on three tiers using prospectively collected primary data entered by clinical staff: (1) number of patients with access to an MTB, (2) proportion with revised diagnostic or therapeutic recommendations, and (3) proportion with implemented changes. Therefore, the study aims to include 4,807 patients (intervention group: 3.507). A mixed-methods approach is employed to evaluate further aspects of the implementation process including patient and staff satisfaction, perceived quality of care, and the degree of harmonization and collaboration within the network. Health economic outcomes include health-related quality of life, healthcare utilization costs, and intervention-related costs.

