## Analysis and anticipated results

### Quantitative evaluation

The hierarchically organized endpoints described above (see Table 2) will be analyzed as binary variables (yes/no) while accounting for cluster effects from the individual centers using generalized estimating equations (GEE) in a logistic regression model (working correlation structure: exchangeable). The study arm (traditional procedure vs. standardized procedure according to the new form of care) will be coded as a binary variable, changing over time for centers newly included in the intervention condition. The Type I error rate will be set at 0.05 (two-sided). *P*-values for the secondary endpoints will be reported, but these should not be interpreted confirmatively. No corrections for multiple testing are necessary. Cluster effects will be addressed using GEE. In the primary analysis, we will use the independence estimation equation, and in a secondary analysis, we will use the exchangeable correlation structure within centers which allows for estimation of the cluster effect.

We expect the intervention to have a measurable impact on patient management as reflected in the primary outcome. Specifically, we anticipate the following effects across three levels of outcome assessment: Level 1, an increase in the frequency of indication-driven, standardized access to the MTB following implementation of the intervention; Level 2, a higher proportion of cases in which the recommendation for further diagnosis or therapy is modified as a result of MTB discussions under the harmonized approach; Level 3, an increase in the proportion of patients for whom the recommended changes in diagnostics or therapy are actually implemented in clinical practice. These analyses (Levels 1–3) will be additionally done with respect to the evidence level of the recommended therapies.

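### Tier 3 of the primary endpoint is defined once among Tier 2 positives and once without that restriction, and the protocol article does not reconcile the two

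*Protocol article*

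**What the plan says.** The primary endpoint, change in patient management after the molecular tumor board, has three tiers.

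**Tier 3**
- Data collection and management, Quantitative evaluation: "Among this group, Tier 3 evaluates the proportion of patients for whom the changes ultimately led to treatment within the framework of personalized medicine". The group meant is the one defined in the sentence before it, the patients changed at Tier 2.
- Outcomes, Table 2: "Tier 3: proportion of patients with an actually implemented changed diagnostic strategy and/or therapy". There is no restriction to Tier 2 positives.
- Abstract, Methods: "2) proportion with revised diagnostic or therapeutic recommendations, and (3) proportion with implemented changes", given as parallel proportions.
- Analysis and anticipated results, Quantitative evaluation: "an increase in the proportion of patients for whom the recommended changes in diagnostics or therapy are actually implemented in clinical practice". This names no denominator.

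**Tier 2**
- Table 2: "Tier 2: proportion of patients with changed diagnostic strategy and/or therapy recommendation due to the decisions of the tumor board".
- Data collection section: "At Tier 2, it will be assessed for which patients the diagnostic process or diagnostic interpretation was significantly changed". Therapy recommendations are not named here.

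The analysis section says that the endpoints "will be analyzed as binary variables (yes/no) while accounting for cluster effects from the individual centers", with no separate analysis set for Tier 3. The Sample size section bases its power on 1,300 control and 3,507 intervention patients and ties it to no particular tier.

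**The concern.** Two things differ between the versions of Tier 3. The first is the denominator: Tier 2 positives in the data collection section, patients without restriction in Table 2 and the abstract. The second is the event. Table 2 counts an implemented change of diagnostic strategy or therapy, while the data collection section asks that the change led to treatment. A patient whose only implemented change is diagnostic is a Tier 3 'yes' in Table 2 and, on the plain reading, a 'no' in the data collection section.

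The denominator matters most. The intervention is meant to raise Tier 2. Restricting Tier 3 to Tier 2 positives therefore selects patients on an outcome that arises after the intervention starts, which can add selection to a comparison that is already non-randomized. The two versions can then differ in sign, and the restricted one rests on fewer patients than the power statement. If the choice is left open until the data are in hand, it can be steered by the results.

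**Working it through.** **Inputs.** From the Sample size section: 1,300 control and 3,507 intervention patients, two-sided 5%, 86% power for 5 points ignoring clustering. The document gives no Tier 2 or Tier 3 rates, so every rate below is an assumption.

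**1. The plan's own figure.** Power = Φ[(d - 1.96·SE0)/SE1], with SE0 from the pooled rate and SE1 from the separate rates. For 47.5% versus 52.5%, SE0 = 0.01623 and SE1 = 0.01622. This gives Φ[(0.05 - 0.0318)/0.01622] = Φ(1.12) = 86.9%, or 86.2% with a continuity correction. The stated 86% is reproduced, and it uses every patient.

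**2. Can the sign differ?** Let q be the Tier 2 rate and c the implementation rate among Tier 2 positives, with 0 for control and 1 for intervention. The all-patient Tier 3 rate is q × c. If the intervention raises Tier 2 (q1 > q0), the two versions have opposite signs whenever c1/c0 lies between q0/q1 and 1.

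Illustration A: q = 40% versus 60%, implemented in 16% versus 21% of all patients.
- All patients: 21% - 16% = +5 points, z = 0.05/0.01290 = +3.88.
- Tier 2 positives: 0.16/0.40 = 40% and 0.21/0.60 = 35%, so -5 points. With 520 and 2,104 patients, z = -0.05/0.02351 = -2.13.
- Check: c1/c0 = 0.875 lies between 0.667 and 1.
- With a variance inflation of 2 (divide z by √2): +2.74 and -1.50.

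Illustration B: q = 40% versus 60%, c = 50% versus 40%.
- All patients: 20% versus 24%, z = +2.93 (+2.07 with inflation 2).
- Tier 2 positives: 50% versus 40%, z = -4.14 (-2.93 with inflation 2).

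**3. Does the power statement carry over?** Suppose the same share passes Tier 2 in both arms. Power for a 5-point difference, unclustered, rates near 50%:

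| Share passing Tier 2 | Control / intervention | Power |
|---|---|---|
| 100% | 1,300 / 3,507 | 87% |
| 60% | 780 / 2,104 | 67% |
| 40% | 520 / 1,403 | 50% |
| 30% | 390 / 1,052 | 39% |

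For 7 points with variance inflation 2 (stated 85%, reproduced as 86%), the values at 60%, 40% and 30% passing are 66%, 49% and 39%.

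The result depends on the rates. If 40% pass and the rates are 15% versus 20%, power is 72%; the full sample at those same rates would have 98%. With the unequal Tier 2 rates of illustration A (520 versus 2,104 patients, 40% versus 35%), it is 57%.

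**The case against.** Table 2 and the abstract do not say that every included patient is in the denominator. The only explicit denominator is the restricted one, and the short lines elsewhere could be abbreviations of it. The analysis section calls the endpoints hierarchical, and its Level 3 wording fits either reading. This stands in part: the unrestricted base is inferred, from the parallel wording of Tier 2 and from the full-sample power. The hierarchy settles nothing, because under both versions a patient needs a Tier 2 change to be a Tier 3 'yes'. The difference in the counted event remains in any case.

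Four stronger readings are tempting, and the documents do not support them.
- *Reversal is to be expected because added recommendations are harder to implement.* No section says so. The Intervention description includes an agreed, structured process for off-label applications, which could raise implementation, and the analysis section expects Level 3 to rise. Reversal is a possibility only.
- *The restriction destroys comparability.* Transition follows readiness, so there was no randomized comparability to lose. The restriction can add selection.
- *Power falls to a definite figure.* The figures rest on assumed rates, and the power statement names no tier.
- *The restricted test is inherently weaker.* If 40% pass in both arms, 47.5% versus 52.5% among them is only 0.40 × 5 = 2 points among all patients, a harder target. What holds is that the stated power does not describe the restricted version.

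The Tier 2 mismatch is the weaker part. The abstract, Table 2 and the analysis section agree that therapy recommendations count, and the data collection section itself mentions therapy as an example of a documented change. Its sentence on genetic counseling follows Tier 3 and broadens the changes without saying which tier it serves.

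Finally, implementation among patients with a recommendation is a legitimate quantity in an implementation study, and a separate analysis plan may name the analysis set. That would not remove two differing definitions from this article.

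**Conclusion.** The point holds as an unreconciled definition of a primary tier, not as missing detail. That the two versions differ in denominator and in counted event follows from the text; that the unrestricted version means every included patient is an inference, though a well-supported one. Following the data collection section as written would condition a primary comparison on an outcome the intervention is meant to change, and would use fewer patients than the power statement.

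The size can only be illustrated: +5 against -5 points from the same assumed data, and 39% to 67% in place of 86% power for 5 points if 30% to 60% pass Tier 2 with rates near 50%. In illustration A the restricted result no longer exceeds 1.96 once a variance inflation of 2 is applied; in illustration B both results still do. Neither is a forecast for this trial.

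**What to change.** Before analysis, use one definition in the abstract, Table 2, the data collection section and the analysis section:
- Tier 3 is yes or no for every included patient, with no recommended change counted as 'no', and with the Table 2 content (implemented changed diagnostic strategy and/or therapy).
- Tier 2 takes the Table 2 wording throughout. State at which tier, if any, a genetic counseling recommendation counts.
- Implementation among Tier 2 positives is reported as a supportive descriptive measure.

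This matches the sample on which power was calculated. It costs wording only, with no new data, since both versions come from the same patient records. The downside is that the conditional implementation rate is no longer a primary quantity. Recruitment is complete, so the choice should be fixed and dated before outcome data are compared between the conditions.
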